**Methods:**

A prospective, longitudinal, single-blind randomized controlled trial will be conducted at the Breast Unit of ASST Rhodense (Milan, Italy). A minimum of 122 female patients, accounting for 20% attrition, with first breast cancer diagnosis scheduled for surgery will be randomized into three groups: treatment as usual (TAU), TAU plus psychoeducational intervention, and TAU plus EMDR R-TEP. Assessments will be conducted at baseline (pre-surgery), post-surgery/pre-psychological intervention, post-psychological intervention, and at 3-month follow-up. Primary outcomes include the Psychological Distress Inventory-Revised and Post-Traumatic Symptom Questionnaire.

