#### Sample size calculation

2.2.4

An *a priori* power analysis was conducted to calculate the minimum sample size required for this study, following established statistical procedures (Perugini et al., 2018; Taccini et al., 2022). The G*Power software (V.3.1.9.2) (Faul et al., 2007, 2009) was utilized to determine the required sample size for repeated measures analysis of variance (ANOVA) with within-between interaction. The research protocol involves four assessment timepoints, with treatment condition as between-group variable (TAU vs. TAU + psychoeducation vs. TAU+R-TEP) and time as within-subject variable (T0, T1, T2, and T3; see dedicated section).

Given the absence of prior studies implementing this specific intervention protocol, conservative a priori parameters were adopted. These were informed by examining previous studies utilizing similar interventions (though not identical), comparable target samples, and similar constructs. The effect size *f* was set to 0.15 (small-to-medium effect size) and the correlation among repeated measures was set to 0.35. Type I error rate probability (*α*) was set to 0.05 (two-sided), and power (1-*β*) was set at 0.80 (Cohen, 1988; Eid et al., 2017; Perugini et al., 2018).

G*Power analysis indicated 80% probability of correctly rejecting the null hypothesis of no significant group-by-time interaction effect with an overall sample of 102 participants (approximately 34 subjects per group). Based on average patient flow to the unit, to account for an anticipated attrition rate of approximately 20%, the study aims to recruit at least 122 patients, ensuring adequate statistical power for the planned analyses.

The three groups will each comprise a minimum of 34 patients: (A) Control group (G1): Patients receiving standard routine psychological support (TAU); (B) Active control group (G2): Patients receiving weekly psychoeducation session plus TAU; (C) Experimental group (G3): Patients receiving EMDR R-TEP intervention plus TAU.

This sample size is highly feasible considering service patient flow while simultaneously permitting statistical analyses generating reliable estimates.

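### The recruitment target of 122 does not cover the stated 20% attrition: it leaves 97 to 98 patients against the 102 required, and about 78–79% power instead of 80% (minor)

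*Protocol article*

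**What the plan says.** Section 2.2.4 (Sample size calculation) of the protocol article sizes the trial for the group-by-time interaction in a repeated-measures ANOVA and arrives at 102 participants, about 34 per group. It then moves to recruitment: "to account for an anticipated attrition rate of approximately 20%, the study aims to recruit at least 122 patients". The same sentence says that this secures adequate power. The section goes on: "The three groups will each comprise a minimum of 34 patients". The abstract (Methods) repeats the target without the word approximately: "A minimum of 122 female patients, accounting for 20% attrition".

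Two other sections fix what happens to patients who are lost. Section 2.4.2 (Timeline and assessments) and section 2.6 (Statistical analysis) both leave dropouts out of the analyses. Sections 2.3.1 to 2.3.3 also remove patients who change treatment, and section 2.6 discards assessment batteries with more than 10% of items missing.

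**The concern.** The 102 is the number that has to be analysed. If a fifth of the recruited patients are lost and lost patients are not analysed, the recruitment target must be the required number divided by the fraction retained. Adding a fifth to the required number gives a smaller figure, and 122 looks like the result of that shortcut. If so, the trial could recruit exactly to plan, lose exactly the share it expects to lose, and still analyse fewer patients than its own power calculation requires. At stake are the power statement in section 2.2.4, the assurance in section 3.3.2 (Strengths) that the sample size secures adequate power, and possibly the minimum of 34 per group.

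**Working it through.** **Inputs, all from section 2.2.4**
- Effect size f: "was set to 0.15 (small-to-medium effect size)".
- Correlation: "the correlation among repeated measures was set to 0.35".
- Measurements: "The research protocol involves four assessment timepoints", so m = 4.
- Groups: k = 3, equal sizes implied.
- Type I error: 0.05. The text calls it two-sided; the omnibus F test uses the upper tail.
- Target power: 0.80.
- Attrition: about 20%.
- Assumption not given in the document: sphericity (ε = 1).

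**Step 1: reproduce the 102.** For the within-between interaction, G*Power uses a noncentral F with
- λ = f² · N · m / (1 − ρ)
- df1 = (k − 1)(m − 1) = 2 × 3 = 6
- df2 = (N − k)(m − 1) = 3(N − 3)

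At N = 102: λ = 0.0225 × 102 × 4 / 0.65 = 14.12, df2 = 297, power 80.7%. At N = 101 power is 80.2%, and at N = 100 it is 79.7%. The smallest N is therefore 101, which becomes 102 for three equal groups of 34. The stated 102 is confirmed.

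**Step 2: reproduce the 122.**
- 102 × (1 + 0.20) = 122.4, which rounds down to 122.
- 102 / (1 − 0.20) = 127.5, which rounds up to 128, or 129 for three groups of 43.

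Only the first form gives the published figure. The second is the one that allows for a 20% loss among those recruited. The shortfall is 128 − 122 = 6 recruits, or 129 − 122 = 7 for equal groups.

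**Step 3: what 122 delivers at 20% attrition.**
- 122 × 0.80 = 97.6 patients, or 97.6 / 3 = 32.5 per group.
- N = 97: λ = 0.0225 × 97 × 4 / 0.65 = 13.43, df2 = 282, power 78.3%.
- N = 98: λ = 13.57, df2 = 285, power 78.8%.

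**Step 4: the attrition that 122 does cover.** 1 − 102/122 = 16.4%.

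**Step 5: check the corrected targets.** 128 × 0.80 = 102.4, and 129 × 0.80 = 103.2, or 34.4 per group. Both keep at least 102.

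**The case against.** Several points can be made for the plan.

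*The effect is small.* Power falls from 80.7% to 78.3–78.8%. The assumed inputs are less certain than that, since the protocol says no earlier study had used this intervention protocol. With a correlation of 0.40 instead of 0.35, 97 patients would give 82.0%; with 0.30, even 102 would give only 77.2%. This stands, and it is why the point is minor. It does not make the published figure right under the inputs that the protocol chose.

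*Both figures are hedged.* Section 2.2.4 gives the attrition as approximate and 122 as a floor. But the floor is presented as sufficient, it covers only about 16%, and the abstract gives 20% without qualification.

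*The minimum of 34 per group may mean patients allocated.* Then 122 / 3 = 40.7 meets it. The sentence can be read that way. The 34 comes from the 102 needed for analysis, so reading it as patients analysed is more natural, but a breach of the minimum follows only on that reading. The power shortfall does not depend on it.

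*A reader might infer that the 20% covers dropout only, so that the other planned exclusions push power well below 78%.* The document does not support that. It speaks of attrition without defining it, and it gives no rate for treatment switching or invalid batteries. Any figure for that further loss would rest on an invented rate.

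*A reader might also suppose that a mixed model on all randomised patients would recover most of the loss for free.* Nothing in the document allows that to be computed. Patients who leave before T2 provide no post-intervention measurement and add little to the group-by-time test, and section 2.4.1 gives patients who withdraw the option of having their data deleted.

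**Conclusion.** The point holds as a minor arithmetic error in a stated figure. The requirement of 102 is sound; the inflation step is not. With dropouts excluded as written, recruiting 122 and losing 20% means analysing 97 to 98 patients with about 78–79% power, not 80%. The size is about two percentage points of power, or six to seven recruits. No estimate, comparison or error rate is biased by it.

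This rests on the protocol's own f, correlation and number of measurements, on sphericity, and on 20% being the whole loss among those recruited. If patients removed for switching or invalid batteries come on top of the 20%, the shortfall is larger, by an amount that the document does not allow to be computed.

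**What to change.** Correct the statement in the abstract and in section 2.2.4, in one of two ways:

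1. Keep 122, and state that at 20% attrition it gives about 97 patients analysed and about 78% power, and that the required 102 (and so 80% power) is kept only if attrition is at most about 16%. This costs one sentence in two places and a slightly less favourable power figure.
2. Replace 122 by 128, or by 129 for equal groups, if the sponsor prefers to keep 80%. This costs six or seven more patients; section 2.2.4 itself describes the present sample as readily feasible given patient flow.

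In either case, add a clause saying whether the 20% includes patients removed after a change of treatment (sections 2.3.1 to 2.3.3) and batteries judged invalid (section 2.6), and say whether the minimum of 34 per group means patients allocated or patients analysed. Neither clarification costs anything beyond the wording.

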#### Randomization and blinding

2.2.5

The study employs a single-blind RCT design. Participant allocation to one of the three groups (TAU vs. TAU + psychoeducation vs. TAU+R-TEP) will follow rigorous procedures ensuring allocation concealment.

First, each participant will be assigned a unique identification code ensuring individual anonymity. Second, group allocation will be conducted through dedicated web-based software (Randomization.com) (Randomization, 2025) by two independent persons meeting the following requirements: (1) external to the project; (2) unaware of study objectives; (3) with no access to participant information; and (4) without mutual contact. If any condition is not met, these individuals will be replaced. This procedure ensures proper allocation concealment. Regarding blinding, participants are blinded to group assignment rationale, while treating clinicians are necessarily aware of intervention type given the nature of psychological treatments. Participants will be assigned to conditions within seven working days from baseline assessment.

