#### Timeline and assessments

2.4.2

According to the flowchart of the study (Figure 1), participants will undergo six different steps.

*Baseline T0* (post-diagnosis, pre-hospitalization, pre-surgery): Participants will complete clinical interview and self-report psychological assessment battery.*Surgery:* participants will undergo breast surgery.*Follow-up T1* (within 1 week post-surgery): Participants will complete clinical interview and repeat self-report instruments to evaluate temporal changes.*Group assignment:* Following T1 assessment, participants will be randomly assigned to one of three groups, then follow their respective 8-week psychological intervention.*Follow-up T2* (psychological intervention completion, within 3 months post-surgery): All participants will complete the psychological assessment battery again to evaluate temporal changes.*Follow-up T3* (within 3 months post-psychological intervention): All participants will complete the psychological assessment battery again.

Participants who withdraw (dropout) from the study will not have their data considered in analyses. However, these individuals will continue receiving treatment benefits from their assigned condition. To ensure complete and optimal data analysis, questionnaires presenting missing data will be excluded from the study (Pozzar et al., 2020) – though participants will continue benefiting from assigned treatment.

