### Outcome measures

2.5

In accordance with study objectives, this research protocol assesses a comprehensive range of psychological outcomes relevant to breast cancer patients, including affective symptoms, trauma-related distress, body image, self-esteem, emotion regulation difficulties, perceived social support, and global psychological functioning.

An anamnestic form will collect sociodemographic variables (age, marital status, education, family composition, employment status, current intimate relationship information), immigration status, alcohol consumption, substance abuse, and notable life events (separation, bereavement, etc.). Additionally, beyond standard clinical interview, temporal changes will be monitored using validated Italian-language self-report instruments.

All assessments will be administered at baseline (T0), after surgical intervention (T1), after completion of the psychological intervention (T2), and at 3-month follow-up from the complention of the psychological intervention (T3) - to evaluate long-term changes.

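### Two randomisation times are stated, and they conflict unless surgery and T1 both fall within seven working days of the pre-surgery baseline

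*Protocol article*

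**What the plan says.** Section 2.2.5 closes with a deadline for allocation: "Participants will be assigned to conditions within seven working days from baseline assessment".

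Three places fix what baseline means. The Methods paragraph of the Abstract lists the visits: "Assessments will be conducted at baseline (pre-surgery), post-surgery/pre-psychological intervention, post-psychological intervention, and at 3-month follow-up". Section 2.4.2 describes Baseline T0 as "post-diagnosis, pre-hospitalization, pre-surgery". Section 2.5 (Outcome measures) says: "All assessments will be administered at baseline (T0), after surgical intervention (T1". In all three, baseline is T0 and lies before the operation. Section 2.4.2 labels T1 a follow-up.

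Section 2.4.2 also gives an ordered sequence: T0, surgery, T1 within one week of surgery, group assignment, T2, T3. On allocation it says "Following T1 assessment, participants will be randomly assigned to one of three groups", after which patients "then follow their respective 8-week psychological intervention". No text that can be read here reconciles this order with the deadline in section 2.2.5. Figure 1, the flowchart, is not available in the text reviewed.

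**The concern.** Staff are given two operative rules for the moment of randomisation, and for many plausible surgical waits they cannot obey both. Which rule they follow changes two things.

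The first is the status of T1. It is the only measurement between surgery and therapy, it is one level of the time factor used for the power calculation (section 2.2.4), and T1 to T2 is named as a possible within-group comparison (section 2.6). Both primary outcomes, the PDI-R and the PTSQ, are self-reports, and patients are blinded only to the reasoning behind their allocation. If allocation precedes T1 and a patient has been told her arm, her T1 ratings can react to it.

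The second is who counts as randomised. Sections 2.4.2 and 2.6 remove dropouts from the analysis. A patient lost between T0 and T1 was never randomised under the section 2.4.2 order, so her loss does not disturb the comparison. Under the section 2.2.5 deadline she may already be randomised, and she is then removed after allocation. If staff mix the rules, both answers differ from patient to patient.

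**Working it through.** The plan gives no figure of its own on this point, so the check sets its time windows against each other.

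**Inputs**
- Allocation deadline: seven working days after T0 (section 2.2.5, with baseline as defined in the Abstract and sections 2.4.2 and 2.5).
- Earliest allocation: after T1 (section 2.4.2).
- T1: at most 7 days after surgery (section 2.4.2). I take day 1 as the earliest, which is an assumption.
- Wait from T0 to surgery, W: not stated anywhere.

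**Step 1: calendar length of seven working days.** Holidays are ignored and T0 is on a weekday. From Monday, Tuesday or Wednesday the window crosses one weekend: 7 + 2 = 9 days. From Thursday or Friday it crosses two: 7 + 4 = 11 days. Call this C.

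**Step 2: when both rules can be met.** Let d be the days from surgery to T1, and allow allocation on the day of T1, the most favourable case. Both rules hold if W + d ≤ C, that is, W ≤ C − d.

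| T1 taken on | C = 9 | C = 11 |
|---|---|---|
| day 7 after surgery | 9 − 7 = 2 days | 11 − 7 = 4 days |
| day 1 after surgery | 9 − 1 = 8 days | 11 − 1 = 10 days |

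The entries are the longest wait from T0 to surgery that satisfies both rules.

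**Step 3: longer waits.** If W exceeds C − d, following section 2.2.5 puts allocation before T1. If W exceeds C, it also puts allocation before surgery. Following section 2.4.2 instead misses the section 2.2.5 deadline.

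**Step 4: what each rule implies for such a patient.**

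| | Section 2.2.5 followed | Section 2.4.2 followed |
|---|---|---|
| T0 | before randomisation | before randomisation |
| T1 | after randomisation, before therapy | before randomisation, before therapy |
| Lost between allocation and T1 | randomised, then excluded | never randomised |

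**Step 5: link to the sample size.** There is none. The stated 102 reproduces from f = 0.15, correlation 0.35, three groups and four timepoints: λ = 0.15² × 102 × 4 / (1 − 0.35) = 14.1, with 6 and (102 − 3) × 3 = 297 degrees of freedom, gives power 0.807 (sphericity assumed). The moment of randomisation does not enter this calculation.

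**The case against.** The strongest reply is that this is a drafting slip. Section 2.4.2 is the timeline section, it sets out six ordered steps, and the Abstract is consistent with that order. Only one closing sentence in section 2.2.5 stands against it, and nothing shows that the sponsor intends to allocate before surgery. That is probably right about intent. But the sentence is an operative rule in the section that governs randomisation, and intent does not remove it.

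Three stronger readings are tempting, and the document supports none of them.

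- A reader might infer that the two rules are flatly incompatible. They are not: with a short surgical wait and an early T1, both can be met. What is missing is any guarantee that they will be.
- A reader might infer that T1 could be contaminated by treatment. Section 2.4.2 and the Abstract both place therapy after T1, and no text starts it earlier. Only the pre-randomisation status of T1 is in doubt.
- A reader might want to put a size in standard deviations on the bias. The document gives no anchor for this. A reaction at T1 also requires that patients learn their arm before T1, and section 2.2.5 sets a deadline for assignment without saying when patients are told. T1 is not named as a covariate. The planned test is the group-by-time interaction, which includes T0, and T0 precedes randomisation under either rule. A shift at T1 could still enter that interaction, but its size cannot be derived from the text.

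**Conclusion.** Wrong as written: an internal contradiction of moderate severity. The two rules agree only when surgery follows T0 by no more than 2 to 10 days, depending on the weekday of T0 and the day of T1. Beyond that, one of them must be broken.

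The number of patients affected is unknown and could be anything from none to all, because no wait from T0 to surgery is stated. The number lost between T0 and T1 is also unknown: the plan anticipates about 20% attrition overall but does not divide it by interval. The effect on T1 scores depends on patients being told their arm before T1. The effect on who counts as randomised needs no such condition; it follows from early allocation together with the exclusion of dropouts. The conclusion rests on reading baseline as T0, which the article's own usage supports throughout.

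**What to change.** Make section 2.2.5 agree with the order in section 2.4.2, either by counting the seven working days from the T1 assessment or by deleting the sentence. Then state that the assignment is generated and released only after the T1 assessment, so that T0 and T1 are both pre-randomisation measures and patients lost before T1 are not randomised. Check that Figure 1 and the registry entry show the same order. There is no need to require a T1 battery without missing items before release; section 2.6 already says which batteries are valid.

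The cost is a sentence or two, with no extra patients, visits or staff. The existing windows allow it: at most 7 days to T1, 11 calendar days to allocation and 56 days of intervention make 7 + 11 + 56 = 74 days if therapy starts promptly, which is inside the three months after surgery allowed for T2. The change should be made before patients are randomised, because allocation under mixed rules cannot be undone afterwards.

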### Interventions

2.3

All three groups will receive psychological sessions twice weekly, conducted individually, in-person, with duration between 60–90 min.

#### Control group (G1): treatment as usual (TAU)

2.3.1

Patients in the control group will receive unstructured psychological support sessions (without pre-established protocol) aimed at: reviewing individual history before and after disease discovery; exploring emotional experiences related to illness; identifying and strengthening individual resources; reducing psychological risk factors; promoting illness acceptance; and enhancing adherence to medical prescriptions and treatments. This approach reflects standard clinical practice in psycho-oncology settings and serves as the reference condition against which structured interventions are compared. TAU does not involve specific psychoeducation protocols or EMDR. However, if ongoing clinical monitoring during the therapeutic course reveals that a patient assigned to TAU would benefit more from a structured intervention (i.e., psychoeducation or EMDR R-TEP), clinicians will prioritize patient wellbeing and provide the most appropriate treatment. In such cases, the participant would be excluded from statistical analyses to maintain methodological rigor – as treatment crossover would violate the original randomized group assignment and compromise between-group comparability.

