### Study aims and hypotheses

1.8

The present research project aims to implement, refine, and evaluate the efficacy of a psychological intervention supporting women affected by breast cancer who have undergone mastectomy or quadrantectomy. To achieve this objective, in addition to the standard psychological support intervention (treatment as usual; TAU), innovative integrated interventions will be applied, including psychoeducational interventions and interventions utilizing the potential of the EMDR R-TEP protocol.

Through a solid experimental methodology implemented as a randomized controlled trial (RCT), the project aims to identify the most effective intervention modalities for providing integrated psychological support to women with breast cancer. In a broader perspective, the study aims to provide a significant contribution not only to the scientific literature in the field but also to clinical practice, contributing to the optimization of clinical practices in oncology.

Specifically, the primary objective of the research is threefold:

To evaluate over time whether the EMDR R-TEP protocol produces clinically and statistically significant improvements in psychological variables of interest, including anxiety, depression, distress, hopelessness, traumatic impact of cancer diagnosis, psychological well-being, and global psychological symptomatology;To assess the relative efficacy of the EMDR R-TEP protocol by analyzing differences in psychological variable improvements compared with the group receiving psychoeducational intervention and a control group receiving routine standard psychological support treatment (TAU);To evaluate on which psychological variables the EMDR R-TEP protocol is capable of producing the greatest changes in terms of well-being, post-traumatic symptomatology, and stability over time.

It is hypothesized that the EMDR R-TEP protocol, combined with standard psychological support, will demonstrate superior efficacy in significantly reducing levels of distress, post-traumatic symptoms, and other psychological symptomatology (e.g., anxiety and depressive symptoms), compared to both TAU alone and TAU in addition to psychoeducation. The relative efficacy over time of the different treatments will be assessed through retest of the questionnaires identified in the assessment battery.

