Regarding potential adverse events, psychoeducational interventions may occasionally elicit emotional activation or transient distress when addressing trauma-related content or body image issues. Clinicians will monitor for such reactions throughout the therapeutic course. Management of adverse events will be handled at clinical discretion – given that the heterogeneity of possible reactions precludes a standardized intervention protocol. All adverse events will be documented in the study database. Should a participant experience recurrent or severe adverse reactions compromising their clinical stability, or when clinically indicated, they will be reassigned to TAU and excluded from statistical analyses – as treatment crossover would violate the original randomized group assignment and compromise between-group comparability.

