### Expected psychological outcomes

3.1

Based on the theoretical framework outlined in the Introduction, both the psychoeducational intervention (G2) and the EMDR R-TEP protocol (G3) are expected to demonstrate superior efficacy compared to TAU (G1), as both structured interventions specifically target core constructs relevant to this population. However, greater improvement is expected for individuals assigned to the EMDR R-TEP protocol at all timepoints, given its specific focus on trauma reprocessing through bilateral stimulation – directly addressing the traumatic underpinnings of psychological symptomatology in breast cancer patients following diagnosis and surgery. While the difference between the two structured interventions may be less pronounced at the earlier timepoint (T2), the superiority of EMDR R-TEP is hypothesized to be most evident at long-term follow-up (T3), in line with the trauma-focused literature and the mixed efficacy results for psychoeducational interventions.

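### The control arm's switching rule is triggered by expected comparative benefit, which is the question the trial randomises, and not by clinical need

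*Protocol article*

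**What the plan says.** The section on the control group (2.3.1) allows a change of treatment "if ongoing clinical monitoring during the therapeutic course reveals that a patient assigned to TAU would benefit more from a structured intervention", the structured interventions being psychoeducation and EMDR R-TEP, that is, the other two randomised arms. In that event "clinicians will prioritize patient wellbeing and provide the most appropriate treatment". The handling in the analysis follows: "In such cases, the participant would be excluded from statistical analyses to maintain methodological rigor".

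Section 2.2.5 says that "treating clinicians are necessarily aware of intervention type given the nature of psychological treatments". Section 1.8 states the hypothesis that R-TEP added to TAU "will demonstrate superior efficacy in significantly reducing levels of distress, post-traumatic symptoms, and other psychological symptomatology", against TAU alone and against TAU with psychoeducation. Section 3.1 adds that "greater improvement is expected for individuals assigned to the EMDR R-TEP protocol at all timepoints".

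The rules for the other two arms (2.3.2 and 2.3.3) are worded differently: "Should a participant experience recurrent or severe adverse reactions compromising their clinical stability, or when clinically indicated, they will be reassigned to TAU". These patients are also excluded from the analysis.

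**The concern.** A rescue rule normally depends on the patient's state, such as deterioration, a safety event or a score beyond a threshold. The control-arm rule depends on a comparison between treatments, namely whether a structured intervention would do more for this patient than TAU. The trial randomises in order to answer that question, and here a clinician who knows the allocation answers it patient by patient.

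Patients in the psychoeducation and R-TEP arms can move only to TAU, so this clause is the only stated way for a comparator patient to receive R-TEP. Its wording governs how many such moves occur, and each has a cost under either analysis. Under the stated exclusion, TAU loses a patient who is probably not a random one. If switchers were kept in the arm to which they were randomised, the contrast between arms would be diluted.

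This is a treatment rule, fixed in the intervention section. A statistical analysis plan could change how switchers are counted, but not who is switched.

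**Working it through.** **1. The triggers side by side.**
- From TAU: expected greater benefit from a structured intervention. No deterioration, score or safety event is named.
- From psychoeducation and from R-TEP: recurrent or severe adverse reactions that compromise stability, or an open clinical-indication clause. The destination is TAU only.

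The authors therefore wrote a clinical trigger for two arms and a comparative one for the third.

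**2. The plan's own power figure.** Section 2.2.4 states "80% probability of correctly rejecting the null hypothesis of no significant group-by-time interaction effect with an overall sample of 102 participants", with f = 0.15, correlation 0.35, alpha 0.05, three groups and four timepoints.
- λ = N·m·f²/(1−ρ) = 102 × 4 × 0.0225/0.65 = 14.12
- df = (3−1)(4−1) = 6 and (102−3)(4−1) = 297
- Power = 0.807, so the stated figure reproduces.

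**3. Analysis as written (switched patients excluded).** The switch rate is unknown, so the counts are illustrations. Assumptions: 34 per arm, a single timepoint, a true TAU versus R-TEP difference of 0.50 SD, clinician judgement correlating r = 0.5 with poor outcome, and the worst-judged patients removed. If a share c of TAU is removed, the retained TAU mean improves by about r·φ(z)/(1−c), where z is the 1−c quantile of the standard normal.
- 3 of 34: c = 0.088, shift = 0.5 × 0.160/0.912 = 0.088, leaving about 0.41
- 7 of 34: c = 0.206, shift = 0.5 × 0.285/0.794 = 0.179, leaving about 0.32

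Simulation at 34 per arm (200,000 trials per cell), including removals from R-TEP under 2.3.3:

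| TAU removed | R-TEP removed | Apparent difference (true 0.50) |
|---|---|---|
| 3 | 0 | 0.42 |
| 7 | 0 | 0.33 |
| 7 | 3 | 0.41 |
| 7 | 7 | 0.50 |
| 3 | 3 | 0.50 |
| 3 | 7 | 0.59 |

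TAU removals alone work against R-TEP, and R-TEP removals work in its favour. The net sign depends on two rates that the protocol does not give.

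**4. If switchers were instead analysed as randomised.** Assume the benefit appears at T2 and T3 only, with arm means a = 0 (TAU), q·d (psychoeducation) and d (R-TEP). The sum of squared interaction terms is then Σ(a−ā)², and λ = 34·Σ(a−ā)²/0.65. Setting f = 0.15 requires Σ(a−ā)² = 12 × 0.0225 = 0.27.
- q = 0.5: d²/2 = 0.27, so d = 0.735
- q = 0 or 1: 2d²/3 = 0.27, so d = 0.636

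If k TAU patients move to R-TEP and receive a share e of its effect, the TAU mean becomes e·d·k/34. For q = 0.5, e = 1, k = 3 the means are 0.065, 0.368 and 0.735. Then Σ(a−ā)² = 0.225, λ = 11.78 and power = 0.718.

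| Psychoeducation effect | Share of R-TEP effect in switchers | k=0 | k=3 | k=7 | k=10 | Average loss per switch to k=10 |
|---|---|---|---|---|---|---|
| equals TAU (q=0) | full | 81% | 77% | 72% | 69% | (80.7−69.1)/10 = 1.2 |
| halfway (q=0.5) | half | 81% | 76% | 70% | 65% | (80.7−65.2)/10 = 1.6 |
| halfway (q=0.5) | full | 81% | 72% | 59% | 49% | (80.7−48.7)/10 = 3.2 |
| equals R-TEP (q=1) | full | 81% | 72% | 57% | 46% | (80.7−46.1)/10 = 3.5 |

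With q = 0.5, the half-effect row also describes switchers who go to psychoeducation. The loss is therefore roughly 1 to 3 points per switch.

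**The case against.** The clause has a natural clinical reading. It starts from what monitoring reveals and puts wellbeing first, and nothing says that stable patients are meant to be switched. A reader might infer that clinicians will move patients because they share the expectation in section 3.1. That passage is the authors' expectation, and the protocol does not attribute it to the treating clinicians. This limits the point to what the wording permits. It does not remove it, because the condition as written is comparative and no other section narrows it.

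A reader might also take a fall in power to 49% as the expected cost. The documents do not support that. The protocol excludes switchers, so dilution arises only once the exclusion is corrected. Ten switches of 34 has no basis in the text. A full R-TEP effect is also generous for someone who switches partway through an 8-week course.

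Nor can the clause be said to favour R-TEP. Excluding poorly responding TAU patients works against it, and the one inflated result in the table (0.59) comes from R-TEP removals, not from this trigger.

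Finally, a need-based trigger would still be judged by a clinician who knows the arm. That stands, and it limits what the fix can achieve.

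**Conclusion.** The concern holds as a defect in the wording of the trigger, and it should be corrected. The control-arm rule lets an unblinded clinician act on the randomised question, and it permits switches that clinical need does not require.

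Its size cannot be fixed from the protocol, because no switch rate is stated. Under the plan as written, 3 or 7 TAU removals with none from R-TEP would turn a true 0.50 SD into about 0.42 or 0.33. This assumes a 0.5 correlation between judgement and outcome, and with R-TEP removals the net direction is uncertain. Under an as-randomised analysis, power falls from 81% by roughly 1 to 3 points per switch, depending on the psychoeducation effect and on how much R-TEP effect a mid-course switcher gains. If switches are rare, the loss is small.

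The exclusion of switched patients is a separate and larger issue. This point remains after that one is corrected, because the trigger determines how many switches there are to handle.

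**What to change.** In section 2.3.1, replace the expected-benefit condition with a clinical-need trigger: clinically significant deterioration or a safety concern. Record the reason for each switch.

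This is a wording amendment with no added patients or visits. Clinicians lose the discretion to switch on expected benefit alone. Rescue for need remains, and TAU patients still have individual psychological support twice weekly (2.3). The change must be reported to the ethics committee and entered in the registry, as section 2.7 requires for relevant modifications.

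It should reduce the number of switches. It does not remove the bias that each remaining switch carries, and it does not replace correcting the exclusion of switched patients. Tightening the open clinical-indication clause in 2.3.2 and 2.3.3 is optional and adds little.
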